## Abstract

**Objective:**

To evaluate the benefits of implementing Bedside Electronic Transfusion Checks (BETC) to patients and value for money at four hospitals at Barts Health NHS Trust.

**Background:**

BETC aims to enhance transfusion safety by reducing errors associated with positive patient identification checks for compatibility, blood sample labelling, and blood component administration. There is limited evidence on the potential benefits to patients and healthcare professionals as well as value for money for implementing BETC.

**Methods:**

The BETC implementation at four hospitals adopted a non‐randomised, staggered, multi‐phase strategy. Alongside the implementation, an evaluation study was conducted. The intervention consists of a portable handheld scanning device and a mobile printer used for printing labels that are attached to the compatibility blood bottles and for verifying the patient's details against blood units prior to blood administration. Eligible patients are those who received blood transfusions or had compatibility tests performed during the evaluation period. The outcomes for evaluation include transfusion‐related errors and cost savings from an NHS perspective. Regression‐based time‐series intervention analyses will be applied to evaluate the impacts of BETC implementation.

**Expected Results:**

The three‐year evaluation includes a 12‐month pre‐implementation period (May 2022 to April 2023) and a 24‐month implementation period (May 2023 to April 2025). All staff involved with bedside transfusion were trained on the new system. Data were collected from different transfusion datasets, process mapping dataset, and Health Economics Inventory dataset.

**Discussion:**

Findings from this evaluation study will provide empirical evidence on the effectiveness and value for money of implementing BETC and will support decision‐making for its wider roll‐out in the UK.

## BACKGROUND

1

Blood transfusion can be a lifesaving treatment used across various clinical settings, such as surgical, medical, and obstetric care.^1^ Transfusion pathway within the hospital is a multistep process intended to provide safe service to patients, considering each critical control step from the laboratory to the patient's bedside to ensure that the right blood is given to the right patient in every time. Errors or omissions in any part of the transfusion pathway can result in the wrong blood being given to the wrong patient, which could lead to ABO‐incompatible transfusions (called ‘Never Event’), with serious clinical consequences for patients.^2^, ^3^, ^4^

National hemovigilance reports have repeatedly demonstrated that human errors occur across the whole transfusion pathway. Errors at the bedside, particularly those involving positive identification of patients (PPI), collection of blood samples for compatibility testing, and the administration of blood, are the most common causes of transfusion errors.^2^, ^5^, ^6^ Therefore, when manual positive identification checks are used at the bedside, national guidelines recommend further safety measures to enhance transfusion safety. These include having two blood samples taken independently of one another to confirm a patient's blood group prior to issuing group‐specific blood components,^7^ and enforcing a zero tolerance for any compatibility testing samples that have not been labelled correctly.^7^, ^8^ Further, pre‐transfusion checks, including PPI, should be performed independently at the patient's bedside by two members of trained staff before blood administration.^9^ Although these measures have improved transfusion safety, they are not fail‐safe.^10^ Moreover, the requirement for second blood samples before transfusion and mandatory second‐clinician verification before administration are associated with potential delay with transfusion and more resources required.

The UK Infected Blood Inquiry exposed critical systemic failures in transfusion safety, which led to severe consequences for patients and their families. It called for stronger safety protocols and technological advancements to prevent future harm.^11^, ^12^ The implementation of electronic bedside checks (BETC) through barcode scanning offers a robust mechanism to enhance transfusion safety.^13^, ^14^, ^15^ By ensuring accurate matching of blood components to the intended patient, the electronic system significantly reduces the risk of transfusion errors,^15^, ^16^, ^17^ thereby improving patient safety and clinical outcomes. The use of BETC for blood sample labelling and for blood administration can reduce the risks of errors at these critical control steps, as well as removing the need for a second compatibility testing sample and for a second nurse to perform PPI checks prior to transfusion.

A few studies^14^, ^15^, ^17^, ^18^ have demonstrated the benefits to patients and hospitals as the results of introducing BETC. However, the evidence of economic benefits to the NHS from implementing BETC is limited. In 2022, Barts Health NHS Trust decided to implement BETC at its four hospitals. Taking advantage of this big investment, an evaluation study was commissioned which aims to assess the effectiveness and value for money of the new electronic bedside checks system. This paper presents the protocol for the evaluation of BETC implementation.

## METHODS AND ANALYSES

2

The implementation adopted a non‐randomised, staggered, multi‐phase design. Regression‐based time‐series intervention analyses and descriptive analyses will be applied to evaluate the impacts of BETC implementation. Research Ethics Committee approval (REC Reference Nr 22/NW/0138) and Health Research Authority approval (Nr 311 676) were obtained.

### 
Pre‐implementation status

2.1

Barts Health NHS Trust comprises four hospitals. Between these, in 2022, ~ 65 000 blood units were administered to ~15 000 patients. The blood transfusion process begins with a clinician's decision to prescribe a transfusion and ends with the administration of the blood unit to the patient. Across the four hospitals, blood transfusion follows a standardised 10‐step procedure, as outlined in Figure 1. Of these, seven steps are currently supported by the electronic system, while step 1 (blood sample collection and labelling), step 9 (blood administration), and step 10 (traceability of the blood unit) are performed manually.

**FIGURE 1 tme70002-fig-0001:**
[figure not shown]
Transfusion process steps under manual and BETC systems. Steps 1, 9 and 10 under the manual system will be replaced by the BETC.

PPI checks must be performed every time for steps 1 and 9. In the manual process, step 1 requires that labelling on the blood sample and the request form is handwritten, where the clinician is required to write the patient's full name, date of birth, hospital number, NHS number, date and time when the sample is taken, and provide his/her signature. For step 9, prior to blood administration, PPI must be performed by two nurses who are required to check that the patient's details on the wristband match those on the blood unit and the compatibility label that is attached to the blood unit. For step 10, clinicians must return the traceability tag attached to the blood unit from the ward to the laboratory, where an individual will enter this information in the transfusion electronic system—this confirms the fate of the unit and is called traceability.

### 
Intervention

2.2

The intervention consists of a portable handheld scanning device (or Personal Device Assistance [PDA]) and a mobile printer. For the sample labelling (step 1), the PDA obtains the patient's details electronically via scanning the patient's 2D barcode on the wristband, which is embedded with the patient's details from the patient's electronic record and, in doing so, supports PPI. The PDA then communicates via Bluetooth with the mobile printer to print the label, which is then attached to the blood sample. For blood administration (step 9), the device uses the same 2D barcode to obtain and verify the patient's details against the compatibility label attached to the blood unit. For traceability (step 10), information on the use of blood is transmitted electronically every time a unit is being transfused using the PDA. It should be noted that the BETC can only be used if patients wear wristbands; consequently, these devices will not be implemented in areas where this was not the case (e.g., the outpatient setting for group and screen [G&S] samples).

The routine clinical care of patients receiving transfusions or needing blood samples will not be altered for the purpose of this study.

### 
Theory of change

2.3

We anticipate the implementation of BETC will lead to a reduction in the G&S blood sample rejection rate due to avoidable mislabelling errors (step 1), thus reducing the frequency of re‐bleeding patients, resulting in less distress for patients, and a reduction in the workload imposed upon the clinical staff to re‐bleed and the laboratory to process the sample. This will subsequently prevent potential delays in blood provision (and other treatments that depend on transfusion, e.g., surgery) and thus have better outcomes for patients.

BETC can potentially eliminate the need for having two G&S blood sample rules and two clinicians to perform independent pre‐transfusion checks prior to blood administration (step 9) and will improve the traceability process (step 10), as transfusion data will be collected in real time through electronic transmission of the information, providing a full audit trail. We expect all these changes will free up staff time, allowing them to perform other important clinical tasks, and as a result improving the productivity of the four hospitals. Furthermore, we expect the BETC implementation to generate savings from material and consumable use because of the reduction in re‐sampling. Ultimately, the implementation of BETC will prompt clinicians to carry out key steps of blood transfusion correctly, thus avoiding wrong blood being given to the wrong patient, which can have detrimental outcomes for patients.

### 
Implementation phases

2.4

The BETC implementation at the four hospitals adopted a non‐randomised, staggered, multi‐phase strategy. The time horizon for the evaluation is 36 months. It includes a 12‐month pre‐implementation period (May 2022 to April 2023) and a 24‐month implementation period (May 2023 to April 2025). The implementation includes three phases:Pre‐Pilot (May 2022 to April 2023): This phase focused on site readiness, addressing all IT requirements for the use of the new system in clinical areas, and preparing training material to accommodate BETC integration.Pilot: The pilot was performed in the Haematology Day Units (HDU) at four hospitals. It allowed the project team to identify and resolve any unforeseen issues that had not been picked up in the pre‐pilot stage. The HDUs were chosen due to the high volume of pre‐planned blood transfusions.Full roll‐out: The main BETC implementation was phased out starting from Hospital 1 (July to November 2023), followed by Hospital 2 (December 2023 to March 2024), Hospital 3 (April to October 2024), and Hospital 4 (November 2024 to April 2025). After the completion of the roll‐out at each hospital, there was a three‐week evaluation period.

The principles of the implementation phases were the same across four hospitals, starting with HDU, followed by clinical wards, and then emergency clinical areas (i.e., the A&E department and theatres). The main part of the implementation included training clinicians on how to use the electronic devices (i.e., PDA and mobile printer) for steps 1 and 9. When 80% of clinical staff were trained in a clinical ward, electronic devices were released to the ward for use. Simulation training videos were developed and made available on the Trust intranet for staff to access. Dummy wristbands and dummy blood units were created for demonstration and to make the staff training reflect real practice as much as possible. After practical training, a competency assessment was obtained from all staff via an interactive PDF document, which included questions to consolidate learning and reinforce key points of the training that had been received.

By the end of the full roll‐out phase, we expect all wards to use the devices for transfusion. Some wards might have started using PDAs for transfusion during the full roll‐out period. We collected data for the PDA uptake at the ward level throughout the 24‐month implementation period.

### 
Study participants

2.5

The target population was (a) any patient who has received a blood transfusion for any reason at four hospitals, (b) any patient who had G&S blood samples taken for compatibility testing for any clinical reason during the evaluation period, (c) all clinical staff involved in taking G&S blood samples or administering blood units to patients at four hospitals, and (d) supervisors who delivered the BETC training sessions to clinicians.

### 
Outcome measures

2.6

A summary of outcome measures, definitions, and data sources are reported in Table 1. Benefits to patients will be measured by the reduction in transfusion‐related errors, as proxied by the following five outcomes:Number and rate of mislabelled samples*.Number and rate of wrong blood in a tube*.Number and rate of patients who receive wrong blood due to errors related to bedside checks**.Number and rate of patients who are misidentified at the point of transfusion**.Number and rate of wrong blood units collected from the fridge due to errors related to bedside checks.

**TABLE 1 tme70002-tbl-0001:** Outcome measures for the evaluation of BETC implementation.

Outcome measures	Definitions	Data sources
Measures for benefits to patients		
Mislabelled samples	Samples contain incorrect information of the patient	Winpath, BloodTrack Manager
Wrong blood in a tube	A G&S sample contains blood from the wrong patient	Winpath, BloodTrack Manager, national hemovigilance scheme
Patients received wrong blood due to errors related to bedside checks	Administration of an incorrect blood unit to a patient due to failure in verifying patient identity and blood group compatibility	DATIX and national hemovigilance scheme
Patients are misidentified at the point of transfusion	A patient is incorrectly identified before receiving a blood transfusion	DATIX and national hemovigilance scheme
Wrong blood units collected from the fridge due to errors related to bedside checks	Incorrect blood units from storage due to failures in verifying patient details and blood group compatibility	DATIX and national hemovigilance scheme
Measures for clinician time saved		
Mislabelled samples	Time spent on G&S sample collection, labelling, analysis and reporting.	Process mapping
Wrong blood in a tube	Time spent on G&S sample collection, labelling, analysis, reporting.	Process mapping
Manually labelling blood samples	Time spent on writing patients' details for G&S labelling	Process mapping
Manually writing post‐administration documents	Time spent on recording transfusion details after blood administration	Process mapping
Having second nurse for blood administration	Time spent by second nurse for compatibility check	Process mapping
Completing traceability documentations	Time spent on documenting and tracking blood transfusion details	Health Economics Inventory
Spillover effect	Time saved from a whole blood transfusion process after implementing the BETC	Process mapping
Measures for savings from material and consumable use		
Mislabelled samples	Material and consumable costs for G&S sample collection and labelling	Health Economics Inventory
Wrong blood in a tube	Material and consumable costs for G&S sample collection and labelling	Health Economics Inventory

**In cases where outcomes 1 and 2 overlap, the events will be counted only once, under outcome 2*.

***Errors that occurred at the point of transfusion, will be counted as outcome 4. Other errors will be counted as outcome 3, that is, ‘errors related to bedside checks’*.

Two types of hospital cost savings, as the results of the BETC implementation, will be assessed.Clinician time saved: Time saving will be generated from six sources including time spent on (1) re‐sampling because of mislabelled samples, (2) re‐sampling because of wrong blood in a tube, (3) manually writing blood sample labels, (4) manually writing post‐administration documents, (5) having a second nurse for blood administration, and (6) completing traceability documentations. Also, the implementation of BECT on steps 1, 9, and 10 might generate a spillover effect to other steps, and as a result save clinician time further.Reduction in material and consumable use: Savings will be generated from re‐sampling because of (1) mislabelled samples and (2) having wrong blood in a tube.

### 
Data collection

2.7

Data will be collected from three sources: (1) transfusion datasets: electronic laboratory databases Winpath and BloodTrack Manager, hospital‐based incident reporting schemes (or DATIX), and reports submitted to the national hemovigilance scheme, (2) Process mapping dataset, and (3) Health Economics Inventory dataset. The process mapping and Health Economics Inventory datasets were developed specifically for this evaluation study.

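### No outcome in section 2.6 counts all patients given wrong blood, so the descriptive results cannot show whether such transfusions fell

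*Protocol article*

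**What the plan says.** Section 2.3 (Theory of change) gives the ultimate purpose of BETC as prompting staff to carry out the key steps correctly, "thus avoiding wrong blood being given to the wrong patient". No cause is attached to that aim. The Background adds that BETC is expected to allow "removing the need for a second compatibility testing sample".

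Section 2.6 measures patient benefit through five outcomes. Four bear on this point:

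- Outcome 2, wrong blood in a tube, is defined in Table 1 as "A G&S sample contains blood from the wrong patient". The unit counted is a sample.
- Outcome 3 is "Number and rate of patients who receive wrong blood due to errors related to bedside checks", defined in Table 1 as "Administration of an incorrect blood unit to a patient due to failure in verifying patient identity and blood group compatibility".
- Outcome 4, misidentification, is defined as "A patient is incorrectly identified before receiving a blood transfusion". It does not require that wrong blood was then given.
- Outcome 5 counts wrong units collected from the fridge.

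A footnote to Table 1 separates outcomes 3 and 4: "Errors that occurred at the point of transfusion, will be counted as outcome 4", and "Other errors will be counted as outcome 3". It still describes the second group as bedside-check errors.

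Section 2.8.1 models only mislabelled samples. The other four outcomes are summarised descriptively by hospital and year.

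**The concern.** The event that matters most to patients is receiving wrong blood. The Background says it can follow from an error anywhere in the pathway. The outcome meant to capture it is conditioned on an attributed cause, and BETC changes how the check behind that cause is done: step 9 moves from two nurses to a device, and the second sample may no longer be needed.

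An outcome conditioned on a mechanism that the intervention alters can fall because events are classified differently, or stay flat while events by another route increase. The footnote adds a second problem. It can move actual mistransfusions into an outcome where they are pooled with errors that were caught in time. Readers who want to know whether fewer patients received wrong blood would have no count to look at, although the evaluation is meant to inform wider roll-out.

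**Working it through.** The article gives no event count, rate, alpha or power for outcome 3, so there is no figure to reproduce. The check sets the definitions side by side.

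**Notation (patients per period)**

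- S: given wrong blood after an undetected sample error at step 1
- L: given wrong blood after an error outside the bedside, such as in the laboratory
- B: given wrong blood after a failed check at step 9
- M: misidentified at step 9, with no wrong blood given

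All wrong-blood transfusions: W = S + L + B.

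**What outcomes 3 and 4 contain under each reading**

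| Reading | Outcome 3 | Outcome 4 | Sum, with B counted once |
|---|---|---|---|
| Label and Table 1, bedside check taken as step 9, footnote not applied | B | M, possibly also B | W − S − L + M |
| Footnote applied, step 1 identity check included as a bedside check | S | B + M | W − L + M |
| Footnote applied, residual rule taken literally as all other errors | S + L | B + M | W + M |

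Outcome 3 equals W under none of the readings. The sum comes closest under the third, where it still exceeds W by M, and outcome 4 as defined does not separate B from M. S cannot be recovered from outcome 2 either, because a sample caught before transfusion and one that led to a transfusion each count as one sample.

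**Sample route, step by step.** Suppose a wrong-blood-in-tube sample is not detected. The unit is issued with a compatibility label carrying the intended patient's details. At step 9 the device compares the wristband with that label (section 2.2), and they agree. That check did not fail, and nobody was misidentified at transfusion. The event is certain to appear only under outcome 2. It enters outcome 3 if the failed identity check at step 1 counts as a bedside check, or if the residual rule is read broadly.

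**Size of a pure shift in classification (assumed counts).** Let W = 10 in both periods, with 8 classed as bedside-check errors before BETC. If k of those 8 are attributed elsewhere afterwards, the change in outcome 3 is −k/8:

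- k = 2: −2/8 = −25%
- k = 4: −4/8 = −50%
- k = 6: −6/8 = −75%

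W stays at 10 in every case. Outcomes 2 or 4 rise to the extent that the moved events are recorded there.

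**The case against.** The strongest reply is that bedside checks are wider than step 9. The Background counts sample collection among bedside errors, section 2.1 requires an identity check at steps 1 and 9, and the Table 1 definition of outcome 3 names no step. With the footnote's residual rule, sample-origin mistransfusions may well belong in outcome 3. This stands as a possible reading. It does not rescue the outcome, because the same footnote then takes step 9 mistransfusions out of outcome 3 and mixes them with intercepted errors.

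Several stronger readings are tempting but not supported:

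- A reader might infer that mistransfusions arising from the sample, wristband or device are simply left out. Sample errors appear under outcome 2, a wrong wristband fits outcome 4 as worded, and a device that fails to verify is not excluded by Table 1.
- A reader might infer that BETC would look safer overall through a shift in cause. Benefit is judged on five outcomes, so that holds only if the moved events are not picked up by the others.
- A reader might infer that cause is assigned by staff who know which system was used. The article does not say who classifies events.

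It is also fair to say that restricting an outcome to errors the intervention targets is a defensible choice for specificity, and that an all-cause count brings in laboratory errors BETC does not touch. That supports keeping the restricted count as a breakdown, but not having it without the total.

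**Conclusion.** The point holds in this form: none of the five outcomes counts all patients transfused with wrong blood, and the label, Table 1 and the footnote do not agree on what outcome 3 contains. Outcome 3 can change through classification alone, and the planned summaries cannot show whether the stated ultimate benefit was achieved. This rests on what the article states, not on detail left to a fuller protocol.

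The 25% to 75% range only illustrates the mechanism on assumed counts; it does not predict the size of any shift. That the mix of causes will change under BETC is plausible from sections 2.2 and 2.3 but not established.

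The consequence is limited to interpretation. Outcomes 3 and 4 are descriptive, so no test, sample size or error rate is affected. The cost savings in section 2.8.2 rest on mislabelling, wrong blood in a tube, staff time and traceability, so no cost input changes either. With no model for these outcomes, though, the definition largely determines what readers will conclude. The change should be made.

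**What to change.** From the same DATIX and national hemovigilance extracts:

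- Report the number and rate of all wrong-blood transfusions, regardless of attributed cause.
- Break that count down by where the error arose: sample (step 1), laboratory, collection, and bedside check at step 9 including wristband or device. Keep the bedside-check subset as one line of the breakdown.
- Report outcome 4 separately by whether wrong blood was given.
- Reconcile the outcome 3 label, its Table 1 definition and the footnote, and state whether the identity check at step 1 counts as a bedside check.
- Base any statement about mistransfusion on the all-cause count.

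The cost is small: a change of definition and tabulation. Both sources are already named for outcomes 3 and 4, and section 2.7.1 states no cause filter on the hemovigilance data. The downside is that the total includes some laboratory errors that BETC cannot affect; the breakdown shows how many.

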#### Transfusion datasets

2.7.1

The Winpath system includes variables relating to G&S blood sampling and rejection, all blood units issued, and blood units transfused. BloodTrack Manager gathers electronic data regarding the use of PDAs, blood fridges, and BloodTrack kiosks. Incidents relating to non‐conformances or near misses relating to transfusion were collected through DATIX, that is, the Trust's incident reporting and risk management software. Adverse events relating to transfusion were collected through the national hemovigilance scheme. We applied the same data collection strategy across the four hospitals, that is, with the same variables extracted from the four datasets and the same time period applied.

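### A fall in outcome 4 counts as patient benefit, but the outcome does not separate misidentifications stopped at the bedside check from wrong transfusions that went ahead, and BETC may change how many errors are noticed and reported

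*Protocol article*

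**What the plan says.** All references are to the protocol article.

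- **Direction of benefit (section 2.6):** "Benefits to patients will be measured by the reduction in transfusion‐related errors, as proxied by the following five outcomes". Outcome 4 is one of the five.
- **Definition of outcome 4 (Table 1):** "A patient is incorrectly identified before receiving a blood transfusion". The listed sources are DATIX and the national hemovigilance scheme.
- **Content of DATIX (section 2.7.1):** "Incidents relating to non‐conformances or near misses relating to transfusion were collected through DATIX".
- **Overlap rule (footnote to Table 1):** "Errors that occurred at the point of transfusion, will be counted as outcome 4". Remaining errors go to outcome 3.
- **What BETC does at step 9 (section 2.2):** "the device uses the same 2D barcode to obtain and verify the patient's details against the compatibility label attached to the blood unit". Section 2.3 adds that BETC may remove the need for two clinicians to make independent checks before administration.
- **Analysis (section 2.8.1):** mislabelled samples are modelled. The other four patient outcomes, including outcome 4, are summarised descriptively at hospital and year level.

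**The concern.** A recorded incident count is the product of two things: how often the error happens, and how likely it is to be noticed and reported. Reading a fall as benefit assumes that the second factor stays constant. At step 9 it may not, because BETC replaces the check at which these errors are noticed. The check moves from two people comparing wristband and label to a device scan, possibly without the second person.

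The wording of outcome 4 also allows two opposite events into one count. An error stopped at the check shows the safeguard working. A transfusion started on the wrong patient or with the wrong unit shows it failing. More of the first may accompany less of the second. If they are pooled, a change in the total cannot be read as better or worse care. Outcome 4 is one of the declared measures of patient benefit in an evaluation meant to inform wider roll-out in the UK, so a yearly table of it is likely to be read at face value.

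**Working it through.** The article gives no event rate, detection rate or target effect for outcome 4, so there is no stated figure to reproduce. The check has two parts.

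**1. Does the text separate intercepted from completed errors?**

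- The Table 1 definition concerns identification before transfusion and does not require that blood was given. Outcome 3, by contrast, is defined by administration of an incorrect unit.
- The source, DATIX, holds near misses.
- The footnote allocates by where the error occurred, not by whether it was stopped. Read literally, a wrong transfusion that arose at the point of transfusion goes to outcome 4, and so does a mismatch caught there. Outcome 3 therefore does not isolate the completed errors.

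No part of the article as shown restricts outcome 4 to errors that got past the check.

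**2. How far can the recorded count depart from the true one?**

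Let *N* be units per year, *m* the true misidentification rate under manual checking, *r* the true proportional reduction with BETC, and *d0* and *d1* the shares noticed and reported before and after.

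- Recorded before = N × m × d0
- Recorded after = N × m × (1 − r) × d1
- Ratio after/before = (1 − r) × d1/d0
- The count rises when d1/d0 > 1/(1 − r)

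The break-even values of d1/d0 are 1/0.75 = 1.33 for a true 25% reduction, 1/0.5 = 2 for 50%, and 1/0.25 = 4 for 75%.

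For illustration, N is about 65 000 units (the 2022 figure in section 2.1). **The values of m, r, d0 and d1 are assumptions and are not in the article.** With m = 1 per 1000 there are 65 000 × 0.001 = 65 true events per year under manual checking.

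| r | d0 → d1 | Before | After | Ratio |
|---|---|---|---|---|
| 50% | 0.1 → 0.9 | 6.5 | 65 × 0.5 × 0.9 = 29.25 | 4.5 |
| 50% | 0.2 → 0.9 | 13.0 | 29.25 | 2.25 |
| 50% | 0.1 → 0.3 | 6.5 | 65 × 0.5 × 0.3 = 9.75 | 1.5 |
| 50% | 0.5 → 0.9 | 32.5 | 29.25 | 0.90 |
| 50% | 0.5 → 0.25 | 32.5 | 65 × 0.5 × 0.25 = 8.1 | 0.25 |
| 0% | 0.5 → 0.25 | 32.5 | 65 × 0.25 = 16.25 | 0.5 |

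The ratios do not depend on m. With m = 2 per 10 000, for example, the second row becomes 2.6 → 5.85, again 2.25.

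In the first five rows the same true halving gives a recorded ratio anywhere from 0.25 to 4.5. In the last row the recorded count halves with no true change. The sign and size of the recorded change are therefore set jointly by r and by d1/d0, and the plan has no means of telling them apart.

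**The case against.** A reader might infer something stronger: that the device logs every mismatch it stops, so a working system will push outcome 4 up and look harmful. The article does not support this.

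- The electronic record described in section 2.3 belongs to traceability (step 10), and section 2.2 ties that transmission to units being transfused. Neither says that a failed step 9 scan is logged as a misidentification.
- BloodTrack Manager, which holds the PDA data, is listed in Table 1 for outcomes 1 and 2 only. A device stop reaches outcome 4 only if someone reports it. If stops are cleared without a report, the bias favours BETC.

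Other fair points reduce the weight of the concern:

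- That near misses enter outcome 4 is inferred from the definition together with the description of DATIX. The article does not say so outright, and some wrong units stopped at the check might instead be filed under outcome 5.
- Figure 2, which links outcomes to proxies in the datasets, is not available here, and detailed incident coding is commonly left to a fuller document.
- Outcome 4 is not modelled or tested. None of the listed sources of savings uses it, and the long-term benefit estimate in section 2.8.4 rests on national hemovigilance data and disutility weights.
- Every detection figure above is assumed.

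All of these stand as limits. They do not remove the core. The definition, the allocation footnote and the direction of benefit are all stated in the article, and applying them as written gives a count whose change has no clear meaning.

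**Conclusion.** The point holds as one of measurement validity. Outcome 4, as worded, may pool intercepted and completed errors, and it is scored as benefit when it falls. BETC may alter both how often errors occur and how often they are noticed and reported. A recorded rise is not evidence of harm, and a recorded fall is not evidence of benefit.

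The direction of bias is unknown, and the documents do not support a claim that BETC will look harmful. The size is also unknown: the ratios of 0.25 to 4.5 under a true halving show what assumed detection shares can do and are not predictions. The consequence is limited to a descriptive hospital-by-year summary. It is worth correcting because that summary is one of the stated measures of patient benefit and no model stands between the raw counts and the reader.

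**What to change.** In section 2.6:

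1. Classify every step 9 event from DATIX or the hemovigilance scheme as intercepted or not intercepted, and by how it was found (PDA alert, human check, later review).
2. Apply the reduction-as-benefit reading only to non-intercepted errors, meaning a transfusion started on the wrong patient or with the wrong unit, and align the footnote on outcomes 3 and 4 with this split.
3. Report intercepted events separately as a measure of detection, with no direction of benefit, and show PDA-alert interceptions on their own for the BETC period.

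The cost is coding the narratives of incident reports that are already being collected, plus a short addition to the text. The downside is that fewer events will count towards the benefit claim, so the yearly figures for non-intercepted errors may be very small. The split does not correct for under-reporting of device stops, but it keeps that uncertainty out of the benefit claim.
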